### 3.4.3 Clinical cohort study

The following outcomes will be determined for the clinical cohort:

- Mortality rate and cause of death
- Adherence rates
- Rate of failure of first-line ART
- Rates of incident opportunistic infections and tuberculosis
- Rates of hospital admission
- Rates of school attendance

In addition, the above outcomes and rate of lung function decline and rates of pubertal development and growth will be compared by ART status.

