## 1.3 Methodology

All children aged 6-15 years attending for acute care at primary health care clinics (PHC) in seven high-density suburbs of southwest Harare will be offered routine HIV counselling and testing during a two year period. The effectiveness of PHC-based routine PITC in providing high coverage of HIV diagnosis will be assessed through a prevalence survey for undiagnosed HIV infection in the 8-17 year age-group in the suburbs served by the PHCs. The seven PHCs will also provide decentralised HIV care, including antiretroviral therapy (ART) initiation.

Children who test HIV-positive through PITC at the PHCs will be recruited into an individual randomised trial of a voluntary lay worker (VLW)-delivered intervention to support households of HIV-infected children aged 6-15 years. Participants will be randomly allocated to either a) primary care based HIV care or b) primary care-based HIV care plus treatment support provided by VLWs, aim, aiming for equal number of control and intervention participants in each clinic. The intervention will be delivered over a eighteen month year period, the main outcomes being adherence to ART, and retention in care.

Children receiving HIV care at the PHCs including those recruited into the trial will be recruited into a clinical cohort study. Data from routine clinic visit (including height, weight, clinical symptoms, incident clinical events and adherence) will be collected. In addition, detailed growth monitoring, lung function testing and a psychosocial assessment (i.e. schooling, guardianship, and disclosure) will be carried out at pre-defined intervals. The rate of lung function decline and rates of pubertal development and growth will be compared by ART status, to investigate whether current ART initiation guidelines can prevent or delay progression of chronic lung disease and/or growth failure.

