## 2.2 Complications of longstanding HIV infection

Late diagnosis in children is associated not only with a risk of the well-recognised HIV-associated infections, but also with risk of chronic conditions that are not manifest in infants or adults. Nearly 50% of older HIV-infected children currently in care have life-threatening chronic lung disease, associated with severe respiratory insufficiency, hypoxia, and cor pulmonale.17-18

We have recently shown that constrictive obliterative bronchiolitis (OB) is the likely major underlying cause.17 OB affects the small airways, causing airflow limitation and hypoxic lung disease. It is difficult to diagnose (requiring high resolution CT scan, not chest radiography), and tends to be irreversible once established. OB can result from a number of insults, including post-adenovirus infection, and is an integral feature of the pathology of cystic fibrosis and rejection following lung transplantation, with some evidence for genetic predisposition to severe forms.19-21 OB has not been recognised in Western cohorts, suggesting either a geographical variability (e.g. due to more frequent exposure to respiratory tract viruses) or that early ART can prevent OB. In our series from Harare, however, OB was not restricted to patients with low CD4 counts and did not appear to respond to ART once established. However, this was a cross-sectional study and little is known about the natural history of this condition.

Pronounced stunting and pubertal delay are also common. Catch-up growth and pubertal development are likely to be age-dependent, with less good outcomes reported when ART is started in older children and adolescents.22-23 Untreated HIV infection is characterised by pronounced chronic immune activation,24-26 and inflammatory conditions appear unusually common in older children, including seronegative arthritis, cerebral vasculitis and uveitis.7 These conditions result in severe disability and functional impairment.

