# OBJECTIVES AND STUDY DESIGN

## 3.1 Study hypotheses

The starting hypotheses are, firstly, that optimised routine HIV testing and counselling of children aged >5 years attending acute primary care services will be sufficient to provide near-complete and timely (before the onset of severe immunosuppression or chronic complications) diagnosis of long-term survivors living in primary care clinic catchment areas within a relatively short period of time. This assumes that almost all HIV-infected children will have one or more consultations for minor illnesses during the two-year intervention period. Secondly, that decentralised HIV care services (to primary care level) are necessary but not sufficient to ensure good adherence and treatment outcomes, because of a constellation of risk factors for default in older survivors of mother-to-child transmission, notably their high risk of maternal orphanhood. Finally, that immediate commencement of ART regardless of CD4 count may be indicated in this age-group (as in infants), because of an otherwise unacceptably high risk of chronic lung disease.

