## 3.2 Objectives

The broad aim of this study to investigate whether a package of services at primary care level will adequately meet the needs of vertically HIV-infected children and adolescents, or alternatively whether further decentralisation to provide community-level HIV testing and/or treatment support is required.

The study has three main components:

1. To investigate whether routine facility-based HIV testing and counselling of children aged 6-15 years attending acute primary care services provides high coverage of timely diagnosis of HIV in the clinic catchment areas.
2. To conduct a randomised control trial comparing a) optimised primary HIV care services alone with b) optimised primary HIV care services plus treatment support provided by VLWs to households with one or more HIV-infected older children.
3. To add serial lung function and anthropometry to the routine follow-up schedule of newly diagnosed children retained in HIV care, in order to investigate the safety of current deferred-start ART guidelines in this age-group (WHO stage 3/4 disease or CD4 count < 350cells/µl).

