**Table 4.3 Data on ART coverage 2011 (National ART programme)**

|  | **ZIMBABWE** | | **HARARE only** | | **STUDY SUBURBS only** | |
| --- | --- | --- | --- | --- | --- | --- |
|  | Children (<15years) | Adults | Children (<15years) | Adults | Children (<15years) | Adults |
| **Eligible for ART** | 2,006 | 19,934 | 96 | 1,750 | 11 | 167 |
| **Ever Initiated** | 44,877 | 477,706 | 8,963 | 97,525 | 1,821 | 9,859 |
| **Transferred Out** | 80 | 1,644 | 7 | 945 | 5 | 27 |
| **Transferred In** | 168 | 1,366 | 9 | 530 | 1 | 44 |
| **Currently On 1st Line ART** | 40,273 | 415,991 | 8,793 | 75,028 | 1,821 | 3,155 |
| **Currently On 2nd Line ART** | 332 | 6,765 | 150 | 4,199 | 62 | 99 |
| **Lost** | 247 | 870 | 61 | 136 | 0 | 14 |
| **Deceased** | 52 | 564 | 5 | 39 | 0 | 4 |

First and second-line treatment options and fixed-dose combinations (FDCs) with scored tablets are available for children. National ART Guidelines criteria (from May 2010) for starting ART in children are summarised below:

1. Paediatric WHO Clinical Stage 3 or 4 disease, irrespective of CD4 count or CD4%
2. Immunological criteria:

| **Immunological marker** | **Age-specific criteria for initiating ART** | | |
| --- | --- | --- | --- |
| **Infant ≤24 months** | **>24-60 months** | **≥5 years** |
| CD4 % | Treat all irrespective of CD4 count/ CD4% | <25% | N/A |
| CD4 count | <750cells/µl | <350cells/µl (as for adults) |

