## 7.2 Cohort study data collection

Patients who test HIV positive and choose to register for HIV care at the PHC will be invited for an initial assessment within a week of diagnosis. The assessment will include:

- Record of social history: Current household structure, family history, type of guardianship, knowledge of HIV status, schooling
- Review of clinical history: HIV testing history, past infections including TB, other significant illness, hospitalisations, HIV testing history
- Clinical assessment: standardised symptom screen, WHO clinical stage
- Examination: standardised clinical examination, growth assessment, lung function assessment
- Tests: CD4 count, blood sample store

Patients will be referred for counselling and started on cotrimoxazole prophylaxis, and followed up two weeks later for assessment of ART eligibility (according to National Guidelines).

Those who are not eligible for ART will be followed up a month after the initial assessment, and then on a three monthly basis. At each visit, patients will have a brief symptom screen and undergo measurement of height and weight. Cotrimoxazole will be given and patients will have brief counselling. If participants start ART during the follow-up period, they will require an additional visit 2 and 4 weeks later, before reverting back to their follow-up schedule.

Those who are eligible for ART will be referred for counselling and started on the recommended first-line treatment. They will be then followed up at 2 weeks, and then monthly for 2 months and three monthly thereafter. At each visit, they will have a brief symptom screen, assessment of adherence, and measurement of height and weight. ART dose will be checked at each visit and adjusted according to weight.

For all participants, a CD4 count, growth and lung function assessment will be performed every 6 months, and psychosocial assessment (knowledge of HIV diagnosis, guardianship, schooling, disclosure to others) and pubertal staging carried out annually.

Participants who miss scheduled appointments will be offered alternative appointments for clinical review at the next available date. All participants will be followed up for 72 weeks. Participants recruited earlier in the study will continue to receive 3 monthly cohort follow-up until the study ends. At the end of the follow-up period, all participants will continue to receive their routine HIV care at the respective PHCs.

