**Table 11.1: Power to detect risk ratio (RR) for outcomes in ART-naïve compared to**

**ART-exposed children for a given proportion of cohort on ART (total sample=300)**

| **Proportion on ART** | **No. on ART** | **Proportion with outcome in ART Naive** | **Proportion with outcome in ART exposed** | **RR** | **Power** |
| --- | --- | --- | --- | --- | --- |
| 60% | 180 | 50% | 35% | 1.4 | 80% |
| 60% | 180 | 20% | 9% | 2.2 | 82% |
| 70% | 210 | 50% | 35% | 1.4 | 80% |
| 70% | 210 | 30% | 16% | 1.8 | 86% |
| 70% | 210 | 20% | 9% | 2.2 | 86% |
| 80% | 240 | 50% | 36% | 1.4 | 86% |
| 80% | 240 | 20% | 9% | 2.2 | 90% |

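### The cohort's comparison by ART status cannot by itself test the deferred-start guideline, because the guideline decides who is on ART and children change group during follow-up

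*Protocol*

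**What the plan says.** Section 3.2 adds serial lung function and anthropometry "in order to investigate the safety of current deferred-start ART guidelines in this age-group". Section 1.3 gives the same purpose for the comparison by ART status: "to investigate whether current ART initiation guidelines can prevent or delay progression of chronic lung disease and/or growth failure". Section 3.4.3 fixes the contrast: the cohort outcomes it lists, including mortality, opportunistic infections and admissions, and also the "rate of lung function decline and rates of pubertal development and growth will be compared by ART status". The hypothesis behind this, in section 3.1, is that "immediate commencement of ART regardless of CD4 count may be indicated in this age-group". Section 1.6 intends the results to inform whether initiation guidelines need revision.

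Section 5.2 leaves the starting criteria to national policy. The criteria in section 4.4 are "Paediatric WHO Clinical Stage 3 or 4 disease, irrespective of CD4 count or CD4" percentage, or, from age 5, a CD4 count below 350 cells/µl. Section 7.2 provides for a change of group: "If participants start ART during the follow-up period", extra visits follow. Section 11.2.3 expects 210 of 300 children on ART. Table 11.1 powers naive against exposed as two groups of proportions, for example "70% | 210 | 50% | 35% | 1.4 | 80" (per cent power), with more outcomes in the naive group in every row.

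**The concern.** Two questions are being answered with one contrast. The third aim in section 1.2 is the effect of ART on lung function and growth. The third component in section 3.2 is whether deferring ART is safe. A comparison of children on ART with children not on ART addresses the first only after disease stage is dealt with. It does not address the second directly, because deferral concerns what happens to children while they wait.

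Under the guideline, children on ART are those who have met the stage or CD4 criterion, and naive children are those who have not. A difference between them mixes the effect of ART with the effect of being further along in disease. Children who cross over add a second problem. Under an ever/never label, their time before ART, and the survival needed to reach ART, are credited to the ART group. A result in either direction could then be read as evidence about the guideline when it reflects how ART was assigned.

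**Working it through.** **1. The plan's own figure.** For the row with 210 on ART, 90 naive children remain (300 − 210). The ratio is 0.50/0.35 = 1.43, printed as 1.4. Alpha and sidedness are not stated; I assume 0.05 two-sided with pooled variance.

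- Pooled risk = (90 × 0.50 + 210 × 0.35)/300 = 0.395.
- SE under no difference = √[0.395 × 0.605 × (1/90 + 1/210)] = 0.0616.
- SE under the alternative = √[0.25/90 + 0.2275/210] = 0.0621.
- z = (0.15 − 1.96 × 0.0616)/0.0621 = 0.47, so power is about 68% against the printed 80%.

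Over the seven rows the same method gives 74, 77, 68, 77, 73, 51 and 65% against 80, 82, 80, 86, 86, 86 and 90%. The ratios reproduce approximately and the powers do not. That is a separate matter, and nothing below depends on it. What matters here is that the table assumes two fixed groups.

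**2. Effect of assignment by disease stage.** Let *r* be the untreated risk in ineligible children, *C·r* the untreated risk in eligible children, and *R* the true untreated/treated ratio in eligible children. If eligibility alone decides ART:

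- risk in the naive group = *r*;
- risk in the ART group = *C·r/R*;
- observed naive/ART ratio = *r* ÷ (*C·r/R*) = ***R/C***.

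C is not in the documents, so I show an assumed range of 1 to 3, with R at the ends and middle of the range planned in section 11.2.3 and Table 11.1:

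| True R | C = 1 | C = 1.4 | C = 2 | C = 3 |
|---|---|---|---|---|
| 1.4 | 1.40 | 1.00 | 0.70 | 0.47 |
| 1.8 | 1.80 | 1.29 | 0.90 | 0.60 |
| 2.2 | 2.20 | 1.57 | 1.10 | 0.73 |

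The effect disappears at C = R and reverses above it. The planned ratio is observed undistorted only at C = 1. High values of C are not possible at every baseline risk: with 30% in naive children, C = 3 implies 90% in untreated eligible children, which is extreme. The right-hand column is a bound, not an expectation.

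**3. Effect of switching under ever/never classification.** A simulation assumed no ART effect, 72 weeks of follow-up, a 20% risk of an event that prevents any later ART start (such as death), 40–50% starting ART at two weeks, and later starts bringing the planned total to 60–80%. Labelling children ever or never on ART gave a spurious naive/ART ratio of 1.25 to 2.26. This favours ART and is similar in size to the 1.4–2.2 the study aims to detect. For outcomes that do not prevent an ART start, this mechanism is weaker, and attributing pre-ART decline to the ART group works against ART.

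**4. The missing comparison.** If the rule is followed, no ineligible child receives ART and no eligible child is deferred. Children with the same CD4 count and stage are then nearly all treated or nearly all untreated. Neither group contains early ART in ineligible children, which is what the third hypothesis concerns.

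**The case against.** The strongest reply is that section 3.4.3 says only that outcomes will be compared by ART status. It does not say that the comparison is unadjusted or that a child's label is fixed. Most outcomes are written as rates, which allows time-updated exposure. Table 11.1 may be only a simplification for power. Adjustment commonly sits in an analysis plan, which is not shown here, so its absence is not counted. This stands, and it rules out saying that the protocol specifies a crude analysis. It does not remove the point: adjustment for CD4 and stage has little overlap to work with, and it cannot supply the missing early-ART comparator.

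A reader might infer that the ART group starts worse and stays worse, because section 2.2 reports that obliterative bronchiolitis "did not appear to respond to ART once established". The same sentence says that it was not restricted to low CD4 counts, and the section warns that the series was cross-sectional. For lung disease C may therefore be smaller. Established disease at baseline is also a matter of level, whereas the outcomes are mainly decline and new or worsening abnormality. This does not make C equal to 1, and it does not carry over to growth, mortality or opportunistic infection.

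The protocol is also part of the way to a remedy. The outcomes box with Figure 1.1 already lists new and worsening lung-function abnormality and growth under a pre-ART care cohort.

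**Conclusion.** The concern holds in this form: the inference stated in sections 1.3 and 3.2 does not follow from the contrast in section 3.4.3, whatever adjustment is added. The groups differ in disease stage by construction, and neither shows the effect of earlier ART in children not yet eligible.

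A reader might go further and infer that the bias must run towards finding that ART does not help and deferral is safe. The documents do not support that. Indication makes ART look worse, while survival to ART start under ever/never classification makes it look better, so the net direction is unknown. Reversal is possible, not shown. Its size rests on C, which is assumed, and on eligibility alone deciding ART: a true 1.4 is seen as 1.0 at C = 1.4 and as 0.70 at C = 2.

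This should be fixed, but it does not threaten the trial. It affects one of the three main components in section 3.2, and the randomised outcomes are unaffected.

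**What to change.** Revise sections 1.3, 3.2, 3.4.3 and 11.2.3, using measurements already scheduled in sections 7.2, 7.5, 7.6 and 7.8:

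- **(a) Deferral question.** Estimate the incidence of new or worsening lung-function abnormality, and the change in height and lung function, during pre-ART time. Count person-time from enrolment to ART start, in line with the Figure 1.1 outcomes box. State that censoring at ART start is informative, because progression triggers ART.
- **(b) ART effect.** Analyse ART as a time-updated exposure, adjusted for CD4, WHO stage, age, baseline value and trial arm. Use within-child slopes before and after ART only for children with enough pre-ART measurements. Eligibility is assessed two weeks after the initial assessment and lung function is six-monthly, so children eligible at enrolment have almost no pre-ART slope.
- **(c) Claim.** Describe (b) as observational, and do not say that the comparison by ART status by itself tests the guideline. Restate the precision in section 11.2.3 for (a) and (b) in place of the fixed-group table.

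The cost is protocol and analysis wording, with no new visits. The downsides should be stated: lower precision in (a), which rests on about 90 never-starters (30% of 300) plus the pre-ART time of later starters; limited overlap on CD4 and stage in (b); and still no early-ART comparator.

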# STUDY POPULATION

## 4.1 Study Suburbs

Each high-density suburb is served by a main Primary Health Care Clinic (PHC) termed “polyclinic”, which provides acute and antenatal care services to the whole suburb. Six out of the ten high density suburbs in Western Harare were purposively selected on the basis that they have a have a high population of children ≤15 years and the polyclinics do not initiate ART to children in the target age-group. The chosen suburbs comprise approximately 194,885 children aged 6-15 years based on estimates from the Zimbabwe 2002 census.

## 4.2 HIV diagnosis and care services

Overall HIV prevalence in adults Zimbabwe has been declining and was estimated at 19.2% in 2011, 23.9% in 2010 and 30.6% in 2009 (National AIDS Council Annual Report, 2011). The adult HIV prevalence was estimated 19.1% in the study area during the 2008 DETECTB Household HIV Prevalence survey[[1]](#footnote-2). Estimates from the 2002 National Census indicated that there were approximately 120,182 children aged less than 16 years (mean 20,030, SD 4,409 children per suburb).

In a survey of 6 primary school located in the study suburbs, HIV prevalence among 6-14 year olds was estimated to be 2.7% (Table 4.1). Based on the DETECTB and School HIV Prevalence Survey estimates, the expected HIV prevalence among 6-14 year olds in the study suburbs was estimated to be approximately 14% of the adult prevalence, and thus estimated to range between 1.6% and 3.3%.

**Table 4.1 HIV prevalence among adults and primary school children in Study Suburbs**

| **Suburb** | **Adult HIV Prevalence (%)**  *(DETECTB Survey 2008)* | **6-14 yrs HIV Prevalence (%)**  *Primary school Survey 2010)* | **Expected HIV Prevalence in 6-14 yr olds (%)** |
| --- | --- | --- | --- |
| Suburb 1 | 18.43 | - | 2.58 |
| Suburb 2 | 18.75 | 2.89 | 2.62 |
| Suburb 3 | 15.34 | 2.09 | 2.15 |
| Suburb 4 | 23.75 | 3.78 | 3.32 |
| Suburb 5 | 18.46 | 2.05 | 2.58 |
| Suburb 6 | 19.99 | - | 2.80 |
| Suburb 7 | 16.59 | 1.79 | 1.66 |
| **Average** | **18.75** | **2.52** | **2.53** |

## 4.3 HIV Testing in Zimbabwe

HIV testing for adults (over the age of 16 years) is available through 1) client initiated testing provided by PSI Free Standing HIV Testing Services nationally and 2) Provider Initiated Testing and Counselling provided by primary and secondary level health facilities.

The Zimbabwean National Testing Guidelines recommend implementation of routine PITC at health-facilities for children and for adults. However, in practice, HIV testing is only offered to healthcare attendees on the basis of either symptoms that are consistent with HIV infection or client request.

Free-standing testing services do not usually offer HIV testing to minors. A person aged below 16 years wishing to have an HIV test, must be in the company of a parent/guardian. Before being offered testing, the parent/guardian (irrespective of whether they are biologically related or not) must be tested first and then give consent for the child to be tested. If the parent/guardian refuses then child will not be tested.

There was an increase in the number of clients who accessed HIV Testing and Counselling services from 837,789 in 2010 to 990,022 in 2011 (National AIDS Council Annual report 2011) (Table 4.2).

**Table 4.2: HIV testing and counselling (National AIDS Council Annual Report 2011)**

|  | **Age (yrs)** | **<15** | **15-19** | **20-24** | **25-29** | **30-49** | **50+** |
| --- | --- | --- | --- | --- | --- | --- | --- |
| **Clients tested** | Male | 37,848 | 40,980 | 67,995 | 78,741 | 148,405 | 49,031 |
| Female | 35,402 | 64,374 | 107,777 | 111,130 | 189,871 | 59,250 |
| Total | 73,250 | 105,354 | 175,772 | 189,871 | 338,276 | 108,281 |
| **Clients testing HIV Positive** | Male | 7,025 | 2,185 | 5,364 | 1,015 | 42,324 | 10,310 |
| Female | 6,142 | 5,070 | 15,891 | 24,343 | 50,691 | 9,690 |
| Total | 13,167 | 7,255 | 21,255 | 36,358 | 93,015 | 20,000 |
| **% HIV Positive** |  | 17.98 | 6.89 | 12.09 | 19.15 | 27.50 | 18.47 |

